## Abstract

**Background:**

Especially children at risk for asthma are sensitive to the detrimental health effects of passive smoke (PS) exposure, like respiratory complaints and allergic sensitisation. Therefore, effective prevention of PS exposure in this group of vulnerable children is important. Based on previous studies, we hypothesized that an effective intervention program to prevent PS exposure in children is possible by means of a motivational interviewing tailored program with repeated contacts focussing on awareness, knowledge, beliefs (pros/cons), perceived barriers and needs of parents, in combination with feedback about urine cotinine levels of the children. The aim of the PREPASE study is to test the effectiveness of such an intervention program towards eliminating or reducing of PS exposure in children at risk for asthma. This article describes the protocol of the PREPASE study.

**Methods:**

The study is a one-year follow-up randomized controlled trial. Families with children (0–13 years of age) having an asthma predisposition who experience PS exposure at home are randomized into an intervention group receiving an intervention or a control group receiving care as usual. The intervention is given by trained research assistants. The intervention starts one month after a baseline measurement and takes place once per month for an hour during six home based counselling sessions. The primary outcome measure is the percentage of families curtailing PS exposure in children (parental report verified with the urine cotinine concentrations of the children) after 6 months. The secondary outcome measures include: household nicotine level, the child’s lung function, airway inflammation and oxidative stress, presence of wheezing and questionnaires on respiratory symptoms, and quality of life. A process evaluation is included. Most of the measurements take place every 3 months (baseline and after 3, 6, 9 and 12 months of study).

**Conclusion:**

The PREPASE study incorporates successful elements of previous interventions and may therefore be very promising. If proven effective, the intervention will benefit the health of children at risk for asthma and may also create opportunity to be tested in other population.

**Trial registration number:**

NTR2632

## Background

Despite current efforts to prevent passive smoking, some people are still being exposed to passive smoke (PS) involuntarily, especially children because they cannot protect themselves. The World Health Organization estimates that about 40% of children worldwide are exposed to PS [1]. Currently, about 25% of the Dutch population 15 years and older smoke [2]. Although we have seen a major decrease in PS exposure in children, children with (heavy) smoking parent(s) and children from socially deprived families are more likely to be exposed [3]. The harmful health effects of PS exposure in children are enormous and include higher risks of respiratory complaints, varying from airway infections like bronchitis and pneumonia, allergic sensitization to allergens and asthma, to even more serious events like sudden infant dead syndrome and meningococcal septic shock [4-7]. Furthermore, the effect of PS exposure on the airways in children is modified by a positive family history of asthma [8,9]. This underlines the importance of effective strategies to prevent PS exposure in children, particularly those with high risk of asthma. The available literature clearly indicates that prevention of PS exposure in children is difficult to achieve. Various intervention strategies have been developed and tested, but the results are mixed. A narrative review of the effectiveness of 36 trials found only 11 trials to be successful in reducing PS exposure in children [10]. However, 23 of the 36 studies showed an overall reduction of PS exposure in children regardless of the group allocation. A more recent review and meta-analysis of 18 trials found a positive intervention effect in 13 studies, with 4 showing a statistically significant advantage for the intervention group [11]. Overall, the trial designs were diverse, ranging from a clinical setting to home-based, different trial durations, and counselling modalities extending from personal behavioural to web-based counselling. Yet, certain elements of intervention studies appeared to be effective. Positive effects on stopping PS exposure in children have been described for behavioural counselling methods, such as motivational interviewing (MI) [12]. MI is a client-centred, directive method for enhancing intrinsic motivation to change by exploring and resolving ambivalence [13]. In a scientific setting, MI outperformed traditional advice in the treatment of a broad range of behavioural problems and diseases [14]. But behavioural counselling alone is probably not enough for an effective, long-lasting intervention effect to prevent PS exposure in children [15,16]. The addition of repeated feedback on children’s urinary cotinine levels to behaviour-changing strategies seemed to reduce the urine cotinine concentrations in children and the proportion of parents quitting smoking [17,18]. Also, brief interventions, even when used with additional information brochures, were not effective [19,20]; indicating that more than one counselling session is needed to increase the effectiveness of interventions towards stopping of PS exposure in children. The development of an effective intervention program to prevent PS exposure in children is challenging. However, an intervention program that incorporates all successful elements of earlier studies may have high chance of being effective.

### Hypothesis

The hypothesis of the PREPASE study (PREvention of PAssive Smoke Exposure) is that an effective intervention towards eliminating or reducing PS exposure in children with a high risk of asthma is possible by means of a motivational interviewing tailored program with repeated contacts focussing on awareness, knowledge, beliefs (pro/cons), perceived barriers and needs of parents, in combination with feedback about urine cotinine levels of the children.

### Aim

The aim of the PREPASE study is to test the effectiveness of an intervention program towards eliminating or reducing PS exposure in children with high risk of asthma.

### Our primary research question is

What is the effectiveness of a motivational interviewing tailored program including urinary cotinine feedback towards eliminating or reducing PS exposure in children with a high risk of asthma (measured 6 months after the start of the intervention)?

In this study, children with a high risk of asthma are defined as children with a positive family history of asthma in the first degree (father/mother/sibling). The children do not have an asthma diagnosis themselves. The intervention is successful if the percentage of parents reporting to eliminate or reduce PS exposure in their children (also checked with the children’s urine cotinine concentration) 6 months after the start of the intervention is significantly higher in the intervention group than in the control group.

### Our secondary research questions are

1. Does eliminating or reducing PS exposure in children persist after the intervention program (measured at 9 and 12 months of follow-up)?

2. What is the effect of the intervention on parents’ active smoking? Will the intervention also lead to smoking cessation?

3. What is the influence of PS exposure in children with high risk of asthma on their lung function, inflammatory markers in exhaled breath and respiratory complaints?

The aim of this article is to describe the PREPASE study design, which could benefit others who are planning comparable intervention programs.

## Methods/design

### Study design

The study is a one year randomized controlled intervention study comparing “care as usual” to an intervention program towards eliminating or reducing PS exposure in children with high risk of asthma delivered by trained research assistants (RA). The study is conducted in South Limburg, Netherlands at the Maastricht University Medical Centre (MUMC+).

### Eligibility

Inclusion criteria to participate in the PREPASE study are families where the youngest child is 0–13 years old and he/she does not has an asthma diagnosis but has a high risk of asthma (father/mother/sibling has asthma) and is exposed to PS at home by at least one parent. Exclusion criteria are: children who are actively smoking themselves, parents and/or children with mental retardation, children with lung diseases such as asthma, or cystic fibrosis, and, families already receiving professional support for smoking cessation.

### Recruitment

#### Self-referral strategies

First, a random sample of 6987 children aged 0–13 years are selected from the community registries of the civil affairs department of three cities (Heerlen, Maastricht and Sittard-Geleen) in South Limburg. Second, 3013 children aged 0–13 years are selected form the Registration Network of Family Practices (RNH Dutch acronym) [21]. All families receive an invitation letter to participate in the study, including an informed consent form, two questionnaires (A and B) and a stamped addressed envelope. Parents who want to participate are instructed to complete questionnaire A for their youngest child and return it to the research group with the informed consent form. Parents who do not want to participate are asked whether they are willing to complete questionnaire B for the purpose of a non-response analysis. Parents are informed that participation is voluntary but in case of no response, a single reminder letter is sent after two weeks. Questionnaire A includes 91 items (see Additional file 1) and is composed of three parts. The first part consists of general questions on family characteristics: gender and birth date of the child, relationship of the caregiver(s) to the child, birth date of the caregiver(s), the number and birth date of siblings, education level and working situation of the caregiver(s), and ethnicity. The second part of the questionnaire inquire about the child’s general and respiratory health using a Dutch version of the ISAAC questionnaire [22,23], and questions concerning physician diagnosed respiratory infections in the past 12 months, vitamin use, gestational age at birth, birth weight, complication(s) during pregnancy, breast feeding, smoking during pregnancy, diagnosis of syndrome(s) or congenital disease(s), day-care attendance, and the presence of physician diagnosed asthma, eczema or hay fever in the biological parents and or siblings of the child. The third part of the questionnaire consists of questions about parental smoking behaviour and passive smoke exposure towards the child. Smoking behaviour of the parents is measured with a standard questionnaire [24]. Questions about PS exposure in children are derived from earlier studies [25,26] and expert opinions from researches in the field, and included sources of PS exposure at home and elsewhere. Questionnaire B consists of 11 items, including gender and birth date of the child, relationship of the caregiver(s) to the child, wheezing and respiratory complaints in the past 12 months, physician diagnosed asthma, PS exposure during pregnancy and currently, and reasons for not participating in the study.

The third source of recruitment is via cohorts from the MIKADO study [27] and the ADEM study [28] from the department of child pulmonology MUMC+. Families that do not meet the eligibility criteria for the MIKADO study or who complete the ADEM study, and in both cases, give agreement to be contacted for other studies receive a letter from the MIKADO or ADEM team asking them if they would like to be contacted to receive information from the PREPASE study.

The fourth self-referral recruitment strategy is done through primary schools in South Limburg. Parents of 32.000 children aged 6–12 years receive an information letter to participate in an electronic survey (see Additional file 1) study regarding respiratory complaints in children in South Limburg. All letters include the web address of the survey and a unique password to log into the website. The electronic questionnaire is similar to questionnaire A, but with minor adjustments. From the ISAAC only questions regarding wheezing and asthma are used. Moreover, questions regarding parental smoking behaviour are limited to PS exposure towards the child. Schools are encouraged to motivate participation. After two weeks, all parents receive a reminder letter through the primary schools of their children. The fifth source of recruitment is through advertisements in local newspapers.

#### Physician based strategies

Since our target group is likely to consist of a more disadvantaged or vulnerable population, physicians working in the paediatric field (general practitioners, paediatricians and doctors of child and youth health care) are asked to select eligible families to participate from their patient registries or actively during consultations [29]. These families receive information from the study through their physicians and are asked by their physicians if they grant permission to be contacted by a PREPASE study team member for more information. Furthermore, registries of all children in South Limburg at the Regional Public Health Service (GGD Dutch acronym) are checked for eligibility (child 0–13 years of age with high risk of asthma and PS exposure at home). Eligible families receive an invitation letter from their physician to participate in the study.

Except for the recruitment through the community registries and RNH, we cannot control if a family is approached more than once. For the analysis, recruitment source is taken into account. Regardless of the recruitment method, all parents are informed that the MUMC+ is testing the effectiveness of a program to prevent PS exposure in children with high risk of asthma, that the program occurs in the home setting and includes non-invasive measurements of the lung function of the children and that all families will receive a financial reward after complete participation. Parents can give permission to be contacted by a member of the research group if they want more information or are interested to participate in the study.

### Randomisation

Eligible families are contacted by phone to ensure eligibility and willingness to participate in the study. Eligible families, after giving written informed consent, are randomized into one of the two groups, the intervention group or control group, with an allocation ratio of 1 (see Figure 1). A database logistic system is made for the study by MEMIC (Centre for data and information management, MUMC+), and includes a randomization system. Families are pre-stratified according to the age of the child, <6 years and ≥6 years, to prevent chance imbalances between the intervention and the control group with respect to age and age-related variables, such as lung function and possible parental attitude towards passive smoking (parents with younger children may evaluate PS exposure differently from parents with older children). Separate randomization lists are generated for each stratum to ensure treatment group assignments are balanced within each stratum.

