**Figure 1 F1:**
[figure not shown]
**Flowchart of the PREPASE study.** BM = baseline measurement. M = Measurement. The first session starts 1 month after the BM and take place once per month during 6 months. The measurements take place every 3 months after the BM.

Blinding of participants or members of the research team for this study is not possible. However, prior to randomization the participants receive limited information on the intervention program. Participants are informed that the study aims at testing a program to help parents prevent PS exposure in their children and to study the relationship between PS exposure and respiratory complaints in children.

After randomization, parents receive more information about their group allocation. All visits are planned for the entire study period, and a confirmation letter is sent to the participants including information and materials with instructions for the urine sampling and lung function measurements in children.

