### Statistical methods

#### Sample size calculation

The sample size calculation is based on the primary outcome measure, the percentage of families eliminating or reducing PS exposure in the intervention group versus the control group after 6 months. Assuming a 10% stopping PS exposure rate (by elimination or reduction) in the control group because of a ‘trial effect’, a clinically relevant difference in stopping rate between intervention and control group of 20% (stopping rate of 30% in the intervention group), a two tailed test with an alpha of 0.05 for the primary outcome, and a power of 80%, a total number of N=126 families is necessary, assuming one child is included per included family. With an anticipated 15% drop-out rate in the RCT, at least 148 families (74 per group) are necessary to test the effectiveness of the intervention.

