#### Statistical methods

The results of the questionnaires are converted into frequencies and percentages for binary and polytomous variables and averages for continuous variables. For descriptive purposes, baseline summary statistics of demographics and outcomes will be tabulated per group. The effect of the intervention will be assessed by comparing the intervention and control group with respect to the percentage of stopping (by eliminating or reducing) of PS exposure in children (parentally reported and verified with the children’s urine cotinine concentration) 6 months after the start of the intervention. The secondary outcome measures will also be analysed for differences between the intervention and control group. Dichotomous outcomes (stopping PS exposure [by elimination or reduction] in children [yes/no]) will be analysed with mixed logistic regression of PS exposure stopping status on treatment group, time and group by time interaction. The analysis will both evaluate the group difference at the primary time point, 6 months, and the group divergence over time. The analysis is an intention-to-treat analysis which includes all randomized families with at least one measurement. Continuous outcomes will be similarly analysed with mixed linear regression. Non-normality of such outcomes will be handled by data transformation, for example a logarithmic or square root transformation in case of severe positive skewness. Given randomized assignment, no confounding is expected except due to dropout, which is accommodated by using baseline variables as covariates and including all randomized children into the outcome analyses (intention-to-treat analysis) using the direct Likelihood approach of mixed regression, which requires no imputation of missing outcome values. The primary outcome eliminating or reducing PS exposure will be tested two-tailed with an alpha of 5%, but secondary outcomes with an alpha of 1% to prevent type I errors due to multiple testing.

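### The protocol appears to randomise families and disclose their group before the baseline home measurement; the order should be stated, baseline taken first, and the two descriptions of the analysis set reconciled

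*Protocol article*

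**What the plan says.** The Randomisation section describes a phone call to confirm eligibility and willingness. It then states: "Eligible families, after giving written informed consent, are randomized into one of the two groups, the intervention group or control group". No home measurement is listed before this step.

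The text under Figure 1 concedes that neither participants nor the research team can be blinded, and says that families get only limited information about the programme before randomisation. It continues: "After randomization, parents receive more information about their group allocation". All visits are then scheduled, and a confirmation letter goes out with "materials with instructions for the urine sampling and lung function measurements in children".

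The baseline measurement is timed only against counselling. The Abstract says "The intervention starts one month after a baseline measurement", and the Figure 1 legend agrees. Its timing relative to randomisation is not given. The notes to Table 2 place the measurements, which include month 0, in both groups of the trial.

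The Statistical methods section uses baseline variables as covariates to deal with dropout. It says that the intention-to-treat analysis "includes all randomized families with at least one measurement", and later in the same paragraph that all randomised children enter the outcome analyses.

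**The concern.** Parents who already know whether they will be counselled may describe their baseline smoking differently, or change it before the first urine sample. Baseline values that can be altered in this way are no longer safe covariates. They are also the natural reference for a reduction in exposure, although the protocol names no reference.

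There is a second route to bias. A family assigned to measurements only may lose interest on hearing its group and leave before the first visit. Such a family has no measurement and falls outside the analysis set. If this happens more in one arm, the comparison is no longer between the groups as randomised. A baseline taken after disclosure cannot be repaired at the analysis stage, so the order matters before enrolment.

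**Working it through.** **1. Order of events, from the text**

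| Step | Where stated | Position |
|---|---|---|
| Eligibility call, written consent | Randomisation | before randomisation |
| Group disclosed | text under Figure 1 | after randomisation |
| All visits planned; urine and lung function materials mailed | text under Figure 1 | described after disclosure |
| Baseline home measurement (questionnaire, urine, lung function) | Table 2, Outcomes | not placed against randomisation |
| Session 1 | Abstract; Figure 1 legend | one month after baseline |

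The baseline visit needs the urine sample and lung function test, and the materials for these are described as sent after randomisation. The described route to the first visit therefore runs through randomisation and disclosure. Figure 1, not shown, could confirm or overturn this.

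**2. The plan's own sample size**

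Inputs from Sample size calculation: "Assuming a 10% stopping PS exposure rate (by elimination or reduction) in the control group", 30% with the intervention, "a two tailed test with an alpha of 0.05 for the primary outcome, and a power of 80"%, and 15% dropout.

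- Average rate in both variance terms: n = 2 × 0.20 × 0.80 × (1.960 + 0.842)² / 0.20² = 62.8, so 63 per arm and 126 in total, as stated.
- The usual formula, with the pooled variance under the null only, gives 61.6, so 62 per arm and 124 in total.
- Dropout: 126 / 0.85 = 148.2, stated as 148 (74 per group).

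The figure reproduces. The present point concerns bias and does not change it.

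**3. Illustration A: loss from one arm before any measurement**

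Assumptions (the documents give none): no true effect, 74 per arm, and k families, all non-successes, leave one arm only. The apparent rate in that arm is p × 74 / (74 − k). Rejection rates use the normal approximation to the two-sided 5% test.

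| True rate p | k | Apparent rate | False difference (points) | Rejection rate |
|---|---|---|---|---|
| 10% | 4 | 10.6% | 0.6 | 5.2% |
| 10% | 7 | 11.0% | 1.0 | 5.5% |
| 10% | 11 | 11.7% | 1.7 | 6.4% |
| 30% | 4 | 31.7% | 1.7 | 5.6% |
| 30% | 7 | 33.1% | 3.1 | 6.9% |
| 30% | 11 | 35.2% | 5.2 | 10.1% |

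The planned control rate is 10%. The 30% rows assume that rate in both arms.

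**4. Illustration B: shifted baseline reporting**

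This applies only if reduction is counted from the baseline report. Assumptions: no true effect, 63 per arm, 10% success, and a fraction f of one arm's non-successes counted as reducers. The rate in that arm is 0.10 + 0.90 f. Rejection rates come from exact enumeration of the two binomials with the uncorrected chi-square test.

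| f | Rate in affected arm | Rejection rate |
|---|---|---|
| 0 | 10.0% | 5.1% |
| 2% | 11.8% | 6.1% |
| 5% | 14.5% | 11.6% |
| 10% | 19.0% | 29.2% |
| 15% | 23.5% | 52.8% |

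The values of f have no source in the documents, and the table takes the shift in one direction only.

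**The case against.** The strongest reply is that the protocol nowhere says baseline follows randomisation, and the missing flowchart may show the opposite. That stands as a limit on certainty. The text still points one way and would need correcting if the intended order differs.

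A reader might infer that the protocol defines reduction against an open-label baseline, so that the false-positive rate could reach 53%. The documents do not support this:

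- The primary outcome section gives no reference value for reducing. It says only that success can come from stopping smoking or from smoking outside the house, which can be read as status at 6 months. On that reading, over-reporting at baseline creates no responder.
- Parental report is checked against the child's cotinine, assayed by a laboratory blinded to group. An inflated answer alone does not raise cotinine. Blinding the assay does not, however, stop parents from changing their smoking before the sample.
- Parents who start changing before baseline would lower the starting value, which works against the intervention if change from baseline is counted.
- Six-month self-report is unblinded whatever the order, so reordering cannot remove reporting bias at the endpoint.

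Nor is every covariate compromised. Age, sex and family history cannot be altered by knowing the arm. Families recruited with questionnaire A or the school survey reported exposure before randomisation, though this does not cover every recruitment route and includes neither cotinine nor lung function.

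Finally, the two analysis-set phrases can be seen as one: in a likelihood analysis without imputation, a family with no measurement contributes nothing. That is correct in practice, but the analysis then does not contain all randomised children, and who is missing may depend on the arm.

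**Conclusion.** The point holds as a strong inference about order, plus a textual mismatch on the analysis set that does not depend on the flowchart. If allocation is disclosed before baseline, the month-0 values that parents can influence (reported exposure, beliefs, smoking before the urine sample) are open to knowledge of the arm, and loss before the first measurement can differ between arms.

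The size of the bias cannot be derived from the documents. At the planned 10% rate, one-sided early loss of 4 to 11 families has a small effect: 5.2% to 6.4% rejection instead of 5%. The larger figures in Illustration B depend on an unstated definition of reduction and on assumed one-directional shifts, and should not be read as estimates. The case for acting is that the change is cheap and that the problem cannot be undone later.

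**What to change.** - State the order of baseline measurement, randomisation and disclosure in the Randomisation section, and make Figure 1 agree.
- Complete the baseline questionnaire, urine sample and lung function before the allocation is run, or at least before it is opened and disclosed. Send the sampling materials to consenting families ahead of that visit. The month between baseline and session 1 leaves time to randomise, inform families and plan the remaining visits.
- If baseline is completed before the allocation is run, every randomised family has at least one measurement. Define the analysis set as all randomised families and remove the competing phrase. If allocation is run earlier but kept closed, say how families who leave before baseline are counted. Later dropout still has to be handled by the model.

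The cost is a change of sequence in the logistics system and letters, plus a few baseline visits to families who then decline randomisation. The targets of 126 and 148 families stay as they are.
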